## Abstract

**Background:**

Australian Aboriginal children experience dental decay at more than twice the rate of non-Aboriginal children. The Select Committee into the Provision of and Access to Dental Services in Australia noted that the rate of potentially preventable hospitalizations was the highest among children aged between 5 and 9 years and was higher among Indigenous Australians and those living in remote locations. The application of a silver fluoride (AgF) solution to decayed surfaces has been shown to be effective in stopping the decay process and reducing the occurrence of new decay but has been tested to a limited extent in the Australian context.

**Objective:**

This study aims to evaluate the feasibility of using the skills of an Aboriginal health practitioner to undertake the application of AgF to carious primary molars to arrest the caries progression and prevent the occurrence of new caries among young Aboriginal children in remote communities.

**Methods:**

This study is a cluster-randomized controlled trial with communities randomized and stratified based on caries level and water fluoridation status. The trial will recruit 640 children (aged between 6 months and 7 years) from 30 communities. Informed consent will be obtained. At baseline, each child in the intervention group will be examined by a calibrated examiner and subsequently by an oral health practitioner who will prescribe to an Aboriginal health practitioner the teeth to be treated with AgF. A formulation with 38% AgF will be applied for 1 minute (0.004 mL per tooth). The control group will be provided with standard minimally invasive care. Participants will be followed annually for 2 years to assess caries arrest and prevention by blinded calibrated examiners. Child oral health–related quality of life and dental anxiety will be elicited through validated questionnaires. Tests of proportions will be used to evaluate the proportion of lesions arrested and the proportion of surfaces at risk that decayed over the follow-up. Multiple logistic regression with appropriate control for clustering of teeth and communities will be used to evaluate caries arrest, controlling for potential confounding factors.

**Results:**

Community engagement has commenced, and data collection protocols have been prepared. Staff specific to the study (eg, Aboriginal health practitioners or workers) are in the process of recruitment. Participant recruitment will commence in March 2026 and conclude in December 2026. Study outcomes will be reported at 12- and 24-month follow-ups.

**Conclusions:**

This study will test the effectiveness and feasibility of a non-oral health professional applying AgF to achieve caries arrest and prevention and validate clinical findings against digital imagery acquired on site. This pragmatic study will inform the development of suitable and accessible models of care for dental service provision in rural and remote communities in Australia.

**Trial Registration:**

Australian New Zealand Clinical Trials Registry (ANZCTR) ACTRN12624000457549p; https://www.anzctr.org.au/Trial/Registration/TrialReview.aspx?id=387518&isReview=true

**International Registered Report Identifier (IRRID):**

PRR1-10.2196/72227

## Introduction

### Background and Rationale

The interim report of the Select Committee into the Provision of and Access to Dental Services in Australia noted that the rate of potentially preventable hospitalizations was the highest among children aged between 5 and 9 years and was higher among Indigenous Australians and those living in remote locations [1]. The higher tooth decay experience of Australian Aboriginal children, in which the majority of the disease remains untreated [2], is believed, partly, to be due to unfavorable visiting patterns to dental care providers, associated with poor accessibility, cost, and the lack of cultural awareness by service providers [3,4]. Australian Aboriginal children experience dental decay at more than twice the rate of non-Aboriginal children. The current models of service delivery are failing to meet the needs, and most decayed teeth remain untreated. The management of dental decay in young children is challenging, and it is commonly undertaken under hospital-based dental general anesthesia.

A recently completed clinical randomized controlled trial (RCT) successfully managed dental treatment of children recommended for dental general anesthesia using minimally invasive dental treatment approaches in a primary care setting (atraumatic restorative treatment [ART] and Hall technique [HT]) [5]. An RCT in remote Aboriginal communities in Western Australia demonstrated improved access to culturally appropriate care with a greater level of dental care provided, with a reduction in the occurrence of new dental decay among preschool-aged children using the ART and HT approach [6]. Although the ART and HT approach improved access to care, it still required an oral health professional team to visit the remote communities and deliver the services. This limits access to services only when the clinical team is in the community and increases the costs of service delivery. The application of a silver fluoride (AgF) solution to decayed surfaces has been shown to be effective in stopping the decay process and reducing the occurrence of new decay but has been tested to a limited extent in the Australian context. The application of the AgF solution is simple, quick, painless, and noninvasive and could be undertaken by an appropriately trained non-oral health professional. A major disadvantage of the use of AgF is the staining of the treated lesion with a dark brown or black color. However, the additional application of potassium iodide (KI) immediately after the application of AgF has been promoted to reduce the staining effects [7,8].

The application of teledentistry and telediagnosis may also offer opportunities to improve service delivery in remote settings by using telecommunication technology to provide oral health care over a distance and diagnoses based on information collected via smartphone technology [9]. Systematic reviews have suggested that diagnostic accuracy in using photographic images for oral diagnosis is comparable to that of traditional clinical examination, and its use may offer opportunities to improve equity and efficiency in service provision in low-income and challenging access settings [10,11].

### Objectives

The principal aim of the proposed study is to evaluate the feasibility of using the skills of an appropriately trained Aboriginal health practitioner or worker to undertake the application of AgF to carious primary molars of young Aboriginal children in remote communities and evaluate the effectiveness and acceptability of AgF, using a 2-arm cluster RCT. It will also validate the use of teledentistry to diagnose and prescribe treatment remotely. The outcomes will be compared with those of the alternative care model using the recently tested ART and HT approach, delivered by an oral health professional team, for clinical outcomes, cost-effectiveness, cost utility, child oral health–related quality of life (COHRQoL), and child dental anxiety. The objectives of the project are as follows:

The first objective is to measure the number of teeth and tooth surfaces with arrested carious lesions and restored at baseline and follow-up. The hypothesis is that *the number of arrested carious lesions will be greater in the intervention group at follow-up.*

The second objective is to measure the number of teeth and tooth surfaces with dental decay and new decay and the number of teeth with dental infections among study participants at baseline and follow-up. The hypothesis is that *the number of children with newly active decay in their teeth and tooth surfaces and new dental infections in the intervention group will not be greater than the specified difference (risk difference) deemed to be a noninferior outcome.*

The third objective is to measure the extent of discoloration in teeth treated with AgF, with or without KI. The hypothesis is that *the extent of discoloration will be less in the intervention group treated with AgF and KI.*

The fourth objective is to measure the change in COHRQoL and dental anxiety using validated measures. The hypothesis is that *the extent and number of children with improved COHRQoL and dental anxiety in the intervention group will not be any less than the specified difference (risk difference) deemed to be noninferior.*

The fifth objective is to evaluate the cost-effectiveness and cost utility of the interventions. The hypothesis is that *the intervention will be less costly with a noninferior outcome.*

The sixth objective is to evaluate the acceptability of the interventions between the 2 groups of participants through focus group interviews using the “yarning” approach [12].

The seventh objective is to evaluate the reliability and validity of diagnosis and treatment prescription using teledentistry. The hypothesis is that the *sensitivity and specificity will be within the published limits for visual assessment of caries*, that is, 0.86 (95% CI 0.80-0.90) and 0.77 (95% CI 0.72-0.82), respectively.

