### Outcomes

The primary outcome of interest is the number of treated decayed teeth at baseline that became arrested at each follow-up period and the number of sound surfaces treated at baseline that became carious at follow-ups, measured by the count of decayed, missing, and filled tooth surfaces. Secondary outcomes will be changes in COHRQoL and child dental anxiety (Table 1).

**Table 1 table1:** Standard Protocol Items: Recommendations for Interventional Trials (SPIRIT) participant timeline.

SPIRIT participant timeline		Enrollment	Allocation	After allocation			Closeout
		–T1^a^		Baseline	12 mo	24 mo	

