### Sample Size

We used the *power* command within Stata (version 15; StataCorp) and data on decay incidence, restorative outcomes, and COHRQoL impacts from the recently completed Kimberley study [6] to estimate the noninferiority sample size. Approximately 61% of the ART restorations were classified as successful (lesion arrestment), and 81% were estimated to be arrested with AgF treatment from published studies [19]; community intracluster correlation was 0.09. Using these parameters at 80% power and an α of .05 and with 30 clusters available (n=15, 50% clusters per treatment arm), the estimated sample size required was 180 in each arm. Allowing for a 25% loss to follow-up each year, the estimated sample size is 320 per arm or 22 children per cluster (rounded up). The sample size will also have 84% power to undertake subgroup analyses to detect a 20% difference in caries arrestment between carious lesions treated with AgF and KI or without KI. A sample size of 40 for the focus group interviews is expected to be sufficient to allow for the elicitation of parent perceptions about the care provided based on our earlier work [20,21].

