### Statistical Methods

#### Statistical Analyses for Primary and Secondary Outcomes

Analyses will be on an intention-to-treat and per-protocol basis. Objectives 1 to 3 will be tested using a test of proportions and logistic regression and negative binomial regression for overdispersed count data, accounting for clustering within individuals and communities. Subgroup objective 4 will be tested using paired tests for pre- and postintervention changes in COHRQol and dental anxiety as well as unpaired tests for between-group differences at baseline and follow-up; multivariable analyses will use generalized estimating equation linear regression to control for teeth and community clustering. Objective 5, economic analyses, will be tested as outlined in the subsequent section. All analyses will be undertaken by analysts who are blinded to group allocation status, and take into account clustering within communities and baseline factors and any baseline intergroup differences. Multiple imputations of missing data will be undertaken to evaluate its impact on the primary and secondary outcomes.

Objective 6 will be evaluated through qualitative analyses of the focus group interviews, with all interviews digitally recorded and independently transcribed. Transcripts will be read, and coding will be undertaken by analysts who are blinded to group allocation status. A thematic analytical approach will be adopted to develop themes and explore the contextual differences among the perceptions, experiences, and beliefs without a strict requirement for a theoretical focus [23,24]. Transcripts will be read multiple times to establish familiarity with the dataset. Two independent reviewers, one of whom will be an Indigenous researcher, will develop a coding scheme of the transcripts and also develop emerging themes. Where disagreement in coding is identified, the differences will be resolved through discussion and consensus. Our approach will broadly follow a reflexive thematic analysis (based on the study by Braun and Clarke [24]), drawing on subjective interpretations of both an Indigenous and a non-Indigenous researcher. The emergent themes will be explored and further refined. Data management will be facilitated using NVivo (version 12; Lumivero). Objective 7 will be evaluated by calculating sensitivity, specificity, predictive values, and receiver operating characteristics, validated against on-site clinical assessment.

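### The primary arrest outcome is a number in the objectives and outcomes but a proportion in the sample size and abstract, and the 80% power applies only to the proportion

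*Protocol article*

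**What the plan says.** The arrest outcome appears on two scales.

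**As a number**
- Objectives, first objective: "the number of arrested carious lesions will be greater in the intervention group at follow-up". The unit is the lesion, and the wording is not limited to lesions present at baseline.
- Outcomes: "the number of treated decayed teeth at baseline that became arrested at each follow-up period". The unit is now the tooth, and the wording is limited to teeth treated at baseline.

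**As a proportion or rate**
- Abstract, Methods: "Tests of proportions will be used to evaluate the proportion of lesions arrested", with multiple logistic regression for caries arrest.
- Sample Size: 61% arrest for the control restorations, and "81% were estimated to be arrested with AgF treatment from published studies".
- Discussion, Anticipated Findings: arrest rates are to be compared between the arms.

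**Both kinds of model**
- Statistical Analyses for Primary and Secondary Outcomes: objectives 1 to 3 share one list of methods, namely a test of proportions, logistic regression and "negative binomial regression for overdispersed count data". None is tied to hypothesis 1.

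**The concern.** A number of arrested lesions and a proportion of lesions arrested are different outcomes. The number is the product of how many lesions a child had, how many were treated and how often treatment worked. Only the last of these is the treatment effect in the sample size.

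Several features of the design let the first two differ between arms:
- Children with or without caries are eligible (Eligibility Criteria). A caries-free child adds a zero to a count and nothing to a proportion.
- The restriction to primary molars stands in the paragraph on the test arm (Intervention Description) and is not repeated for the control arm, so the number of teeth treated could differ in either direction.
- Only 30 communities are randomised. Stratification by caries level reduces imbalance in lesion burden but does not remove it.
- AgF is reapplied at 12 and 24 months. As hypothesis 1 is worded, lesions that arise after baseline and are later arrested would count.

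Two things are at stake: whether the stated power applies to the primary outcome as defined, and whether the choice between scales that can give different answers stays open until the data are in.

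**Working it through.** **1. Reproduce the stated sample size.** Inputs from Sample Size: 0.61 v 0.81, 15 clusters per arm, "community intracluster correlation was 0.09", "at 80% power and an α of .05". Sidedness is not stated; two-sided is assumed.
- Uncorrected: n = [1.96√(2 × 0.71 × 0.29) + 0.8416√(0.61 × 0.39 + 0.81 × 0.19)]² / 0.20² = 79.6.
- With continuity correction: (79.6/4)[1 + √(1 + 4/(79.6 × 0.20))]² = 89.3, rounded up to 90 per arm.
- Clustering: m = 90(1 − 0.09)/(15 − 90 × 0.09) = 81.9/6.9 = 11.87, rounded up to 12 per community; 15 × 12 = **180**.
- Loss to follow-up: 180/0.75² = **320**.

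Both stated figures are matched exactly. The calculation uses no mean or spread of lesions per child, so it is a calculation for a proportion.

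**2. The same effect as a count.** With equal lesion numbers, 61% v 81% is a count ratio of 0.81/0.61 = 1.328, log 0.284. The design effect is 1 + 11 × 0.09 = 1.99, so the effective number is 180/1.99 = 90.45 per arm.

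Assume μ lesions per child and negative binomial dispersion a (variance = mean + a × mean²). The 0.09 is borrowed here from the arrest calculation. Then SE = √{[1/(0.61μ) + a + 1/(0.81μ) + a]/90.45}.

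For μ = 4, a = 1: SE = √(2.718/90.45) = 0.173; 0.284/0.173 − 1.96 = −0.32; power about 37%.

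**3. Range over assumptions.** The article gives neither μ nor a.

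| Setting | Power |
|---|---|
| Count, unadjusted, analytic: μ 1–6, a 0.2–3.3, count ICC 0.09 | 14–82% |
| Same, count ICC 0 | 23–98% |
| Count, unadjusted, simulated: μ 2–6, a 0.5–2, SD of log community burden 0.25 | 25–45% |
| Count, unadjusted, simulated: μ 4, a 0.5–1, no community variation in burden | about 50–60% |
| Count adjusted for community mean baseline lesions, same settings as the 25–45% row | 84–93% |
| Proportion, same settings as the 25–45% row | 88–96% |

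The simulations use 15 v 15 communities of 12 children, ICC 0.09 for arrest, all baseline lesions treated, and tests on community means.

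**4. Equal arrest, unequal lesions.** If both arms arrest the same share and one treats 1.33 times as many lesions, the expected count ratio is 1.33, the planned effect. With an assumed coefficient of variation of 1.2 and ICC 0.09, SE = √(2 × 1.44/90.45) = 0.178, and 0.284/0.178 − 1.96 = −0.37. The count would be declared greater in about 36% of trials. Simulation at 70% v 70% arrest gives about 35% at mid-range settings (μ 4, a 1), against 2–3% for the proportion and 2–3% for the count adjusted for baseline lesions.

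**The case against.** The strongest reply is that the article never commits to a raw-count test of arrest. The abstract assigns tests of proportions and logistic regression to arrest, the discussion compares arrest rates, and the statistical methods list the proportion test and logistic regression first. Negative binomial regression may be meant for objective 2, which supplies genuine counts of decayed surfaces. A missing offset is detail that a condensed article may leave to a fuller document. This stands: a reader might infer that the trial will run a count test with 25–45% power, and the text does not support that.

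Second, the statistical methods promise to account for baseline factors and baseline differences between groups. Baseline lesion number is the obvious such factor, though it is not named. Adjusting for it restores power to 84–93% and removes the false wins. This also stands, and it limits the harm.

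Third, a chance excess of 33% in lesion burden is uncommon: about 1–8% of trials under the same assumptions. Without a systematic excess, even the unadjusted count keeps its nominal error. The 35–36% figures therefore describe a systematic difference in lesions treated, for which the article gives no figure.

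Fourth, the Outcomes section already limits the primary arrest outcome to teeth treated at baseline. Only the looser wording of the first objective lets later lesions in.

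None of this removes the conflict. The primary outcome and hypothesis are stated here, on a scale other than the powered one, and an analysis plan written to that wording would inherit the count.

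**Conclusion.** The point holds as an inconsistent definition of the primary arrest outcome. The objectives and outcomes state a number, the unit moves from lesions to teeth, the sample size and planned arrest comparison use a proportion, and no model is named for hypothesis 1. That the 80% power is for the proportion is firm, because 180 and 320 follow exactly from the article's own inputs under a two-sided, continuity-corrected calculation.

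The loss from using a count is not firm. The 25–45% depends on assumed lesion means, dispersion, a borrowed ICC, between-community variation in burden and no baseline adjustment. Other assumptions give 14–82%, or more at a lower count ICC. A reader might also infer that lesion imbalance is likely to produce a false win for AgF. The documents do not support that either: randomisation is stratified by caries level and baseline adjustment is foreseen. What remains is a primary outcome that, read literally and left unadjusted, can differ between arms through lesion burden or number of teeth treated alone.

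**What to change.** - **Objectives (first objective) and Outcomes:** define arrest as the proportion of decayed lesions recorded and treated at baseline that are arrested at follow-up. Teeth would serve equally well, but choose one unit and use it throughout. This excludes lesions that arise later.
- **Statistical Analyses for Primary and Secondary Outcomes:** name the cluster-adjusted binomial or logistic analysis of that proportion as the test of hypothesis 1. If negative binomial regression is kept for arrest, make it secondary, with log(baseline treated lesions) as offset.

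The cost is a change of wording in three places. No new data are needed, since tooth surfaces are already charted at baseline, and the sample size is unchanged because it was computed for this proportion. The change should be made before outcome data exist.

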## Methods

### Trial Design

This study will use a robust, pragmatic, 2-arm parallel group cluster randomized, active-controlled, noninferiority trial design. This study will be reported according to the CONSORT (Consolidated Standards of Reporting Trials) guidelines on reporting of noninferiority trials [13]. Study communities will be randomized into test or control groups by a central study coordinator through a computer-generated block randomization procedure, stratified by expected decay experience and exposure to community water fluoridation levels based on findings from our earlier work in the Kimberley region [6]. Both arms of the study will be provided with dental care; the control arm will be treated using the ART and HT approach, and the test arm will be treated using AgF. The test group will be further randomized into 2 groups via computer-generated allocation in concealed envelopes at study sites to receive 1 of the 2 AgF formulations. One formulation will have 38% AgF and KI as a staining reducing agent (Riva Star Aqua; SDI Limited); the other formulation will have 40% AgF with stannous fluoride as a reducing agent (Creighton Dental AgF; Whiteley Corporation). The Riva Star Aqua group will be further randomized to receive KI or no KI to evaluate KI’s effect on reducing the staining associated with AgF and evaluate its impact on caries arrestment. Moreover, we will evaluate the COHRQoL [14] and child dental anxiety and undertake an economic evaluation of the interventions. Focus group interviews, using the yarning approach, will be conducted to better understand the impact of the dental treatments [12]. We will also test the effectiveness of teledentistry in caries diagnosis and treatment prescription. Participants will have digital images taken of their dentition with a smartphone using standardized procedures [15]. The images will be stored and sent securely to a calibrated assessor at a remote site. The assessor, blinded to group allocation, will evaluate the images and diagnose and prescribe treatment.

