### Data Collection and Management

#### Plans for Assessment and Collection of Outcomes

Treated teeth with intact, sound fillings will be assumed to have arrested decay. The changes will be evaluated through a count of decayed, missing, filled, and arrested decayed tooth surfaces at baseline and 12- and 24-month follow-ups using the International Caries Detection and Assessment System criteria [22]. The assessment will be undertaken by calibrated examiners. Color changes of AgF-treated or AgF- and KI-treated lesions will be evaluated through the classification of the treated lesion into 4 categories according to Pantone color plates. Data will be collected through direct data entry using the REDCap (Research Electronic Data Capture; Vanderbilt University) implementation on iPads (Apple, Inc). The Aboriginal research assistant will assist parents, carers, and children whose primary language is not English in completing the questionnaire.

Parents of the study participants will be invited to take part in focus group interviews at the 12-month follow-up. Consenting parents will be interviewed by the Aboriginal research assistant using a semistructured interview schedule, and the interviews will be digitally recorded. The structured open-ended questions will elicit responses from parents on the care received by their child and follow a yarning approach [12]. The questions will be based on the following:

What were some of the positive aspects of dental care experienced by your child?What were some of the negative aspects of the dental care received by your child?Can you give some examples of what you think could have been done and implemented better during your child’s treatment?Can you name some aspects of the setting, location, and process that you think could have been improved?Can you identify any changes to your oral health knowledge since the research began?

We will also take digital images of the teeth of selected children who provide consent to have the images of their teeth recorded using a smartphone and a standardized protocol [15]. The images will be sent via email, using a secure protocol used within the Western Australia Health Department, to a remote site where an independent, calibrated assessor will assign scores to the images using the same criteria as the field assessment.

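### The teledentistry hypothesis sets upper as well as lower limits on sensitivity and specificity, so a remote reader in full agreement with the on-site examiner would fail it

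*Protocol article*

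**What the plan says.** The Objectives section states the seventh objective as evaluating both reliability and validity of remote diagnosis and prescription. Its hypothesis is that "sensitivity and specificity will be within the published limits for visual assessment of caries", and the limits are printed as "0.86 (95% CI 0.80-0.90) and 0.77 (95% CI 0.72-0.82), respectively".

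Under Statistical Analyses for Primary and Secondary Outcomes, the method is: "Objective 7 will be evaluated by calculating sensitivity, specificity, predictive values, and receiver operating characteristics, validated against on-site clinical assessment".

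Under Plans for Assessment and Collection of Outcomes, calibrated examiners score the teeth on site "using the International Caries Detection and Assessment System criteria". An independent remote assessor scores the images by those same criteria.

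Three sections say who is imaged:
- Trial Design: "Participants will have digital images taken of their dentition with a smartphone using standardized procedures".
- Recruitment places image-taking in the baseline examination that follows signed consent, without mentioning selection.
- Plans for Assessment and Collection of Outcomes: "We will also take digital images of the teeth of selected children who provide consent".

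**The concern.** A hypothesis of falling *within* an interval is two-sided. For an accuracy measure only the lower side is of interest, because a sensitivity of 0.95 or a specificity of 0.90 is a better result and not a failure. Here the point is sharper, because remote and on-site readers use the same criteria, so complete agreement is attainable in principle and is the best possible result.

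A second difficulty concerns what the limits describe. They are presented as the accuracy of visual assessment of caries. The on-site reference, scored by calibrated examiners with the International Caries Detection and Assessment System, appears to be a visual assessment too. How accurate a method is does not naturally serve as a target for agreement with that same method.

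Validating remote diagnosis and prescription is a stated aim, and the Discussion links it to wider use of teledentistry. A criterion that rejects a very good reader would either give the wrong answer or be reinterpreted once the data are seen.

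**Working it through.** **Inputs from the protocol article.** Sensitivity limits 0.80-0.90 and specificity limits 0.72-0.82 (Objectives); reference standard the on-site assessment (Statistical Methods); same scoring criteria for both readers (Plans for Assessment and Collection of Outcomes). The limits are quoted from a cited source and no sample size is given for objective 7, so there is no figure of the plan's own to reproduce.

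**Step 1: full agreement against the stated limits.** If every remote score matches the on-site score, sensitivity = specificity = 1.00. Since 1.00 > 0.90 and 1.00 > 0.82, both parts of the hypothesis fail. This needs no assumption about prevalence or sample size. The Abstract and Discussion word the comparison in the other direction (images validating the clinical findings), but full agreement is still 1.00/1.00.

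**Step 2: chance of meeting the hypothesis by true accuracy.** Assume n diseased and n sound units, independent of one another, and apply the limits to the observed values. With X ~ Bin(n, Se) and Y ~ Bin(n, Sp),

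P(success) = P(0.80n ≤ X ≤ 0.90n) × P(0.72n ≤ Y ≤ 0.82n).

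| True Se/Sp against on-site | n=50 | n=100 | n=200 | n=400 |
|---|---|---|---|---|
| 0.86/0.77 | 0.53 | 0.71 | 0.88 | 0.98 |
| 0.90/0.82 | 0.30 | 0.29 | 0.28 | 0.27 |
| 0.92/0.85 | 0.12 | 0.07 | 0.02 | 0.005 |
| 0.95/0.90 | 0.006 | 0.0003 | 0.00 | 0.00 |
| 1.00/1.00 | 0 | 0 | 0 | 0 |

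Once true accuracy exceeds the upper limits, both better reading and more data reduce the chance of success. With lower limits only, the 1.00/1.00 reader passes with probability 1. Clustering of surfaces within children would change the intermediate figures but not the last row.

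**Step 3: the imperfect reference, for illustration only.** Suppose 0.86/0.77 were the on-site examiner's accuracy against true disease. The document does not say this. Let p be the prevalence of decayed surfaces. A remote reader who is always right about true disease would then show

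apparent Se = 0.86p / [0.86p + 0.23(1−p)]; apparent Sp = 0.77(1−p) / [0.77(1−p) + 0.14p].

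- p = 0.30: 0.258/0.419 = 0.62 and 0.539/0.581 = 0.93. Sensitivity is too low and specificity too high.
- p = 0.50: 0.430/0.545 = 0.79 and 0.385/0.455 = 0.85. Again both fall outside.
- p = 0.60: 0.516/0.608 = 0.85 and 0.308/0.392 = 0.79. Both fall inside; this holds for p of about 0.55 to 0.68.

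A remote reader exactly as accurate as the examiner, with independent errors, shows at p = 0.30 a sensitivity of (0.3×0.86² + 0.7×0.23²)/0.419 = 0.62 and a specificity of (0.7×0.77² + 0.3×0.14²)/0.581 = 0.72. With errors half-correlated (joint probabilities midway between independence and complete dependence), the values are 0.81 and 0.86. The answer therefore moves widely with prevalence and error correlation, neither of which the document gives.

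**Step 4: objective against named statistics.** The objective promises reliability and validity. Sensitivity, specificity, predictive values and receiver operating characteristics all describe validity against a reference; none is a reliability statistic.

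**The case against.** The authors may simply have meant at least as good as published visual assessment, in which case one changed word repairs the hypothesis. The planned statistics will be reported whatever the hypothesis says, and no sample size or primary analysis depends on it. All of that stands, and it keeps the point modest. But the text prints upper limits and does not say that they are to be ignored.

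A reader might infer three stronger things that the document does not support.

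- *Any perfect remote reader would fail.* This is certain only when perfect means full agreement with the on-site reference. A reader perfect against true disease would, on the illustrative model, meet both limits at a prevalence of about 55-68%.
- *The trial's examiners miss 14% of decay and over-call 23%.* The article does not give the reference standard behind the published figures, and these are not measurements of this trial's calibrated examiners. Independent errors are also the unfavourable case. Two readers of the same teeth using the same criteria may well share errors, and the half-correlated example clears both lower limits.
- *The criterion errs in both directions.* The examples show good readers failing. None shows a poor reader passing.

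How confidence limits enter the rule, and how clustering is handled for this objective, are matters that an article may leave to the analysis plan. They are not part of this point.

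**Conclusion.** The concern holds for the two-sided criterion. As worded, full agreement with the on-site examiner fails the hypothesis at any sample size. Above 0.90 and 0.82, better agreement makes success less likely (for a true 0.92/0.85, from 0.12 at n = 50 to 0.005 at n = 400 per group). The first statement rests only on the printed limits and the stated reference. The probabilities also assume independent units, equal numbers of diseased and sound units, and limits applied to the observed values.

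The mismatch between benchmark and reference is a fair secondary criticism, but its size is unknown. It depends on prevalence, error correlation and an unstated reference standard, and that the on-site assessment is visual is itself inferred from the scoring system. The missing reliability statistic and the differing accounts of who is imaged are smaller gaps in the same objective. None of this affects the primary comparison or its sample size.

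**What to change.** 1. Restate the hypothesis of objective 7 as one-sided: sensitivity no lower than 0.80 and specificity no lower than 0.72, with no upper limit.
2. State that the on-site assessment is an imperfect reference. Lower limits alone do not cure this: in the 30% illustration, a reader perfect against true disease still shows a sensitivity of 0.62. A shortfall should therefore not be read automatically as poor remote reading.
3. Add an agreement statistic for the reliability part, such as weighted kappa with positive and negative agreement between remote and on-site scores. Read it alongside the on-site inter-examiner agreement from calibration.
4. Reconcile Trial Design, Recruitment, and Plans for Assessment and Collection of Outcomes on which children are imaged. If they are selected, say how, because selection changes the case mix and so the planned predictive values.

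The cost is wording plus one further statistic on scores already planned. The Results section says that examiner calibration is in progress and that recruitment is planned from March 1, 2026, so on that timetable the change can be made before any images are taken.
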